### Safety Parameters and Description of Risk

All the mental health outcomes being assessed are self-reported by participants directly into the study database. The principal investigator or delegate and study coordinator will be immediately alerted through an automated REDCap algorithm when (1) an individual self-reports as having suicidal ideation >0 on question 9 of the PHQ-9 or (2) an individual intentionally does not fill out the suicidality question on the PHQ-9. The principal investigator, delegate, or study coordinator will contact the participant’s endocrinologist or the endocrinologist on call, who will conduct a same-day risk assessment using the Ask Suicide-Screening Questionnaire (ASQ) [49]. If the participant is judged to have acute suicidality or suicidal ideation as per the ASQ, the assessor will either suggest a referral to the emergency department or contact the psychiatrist on call, who will suggest clinical follow-up as appropriate. The assessor will report the results of the ASQ screening back to the study coordinator within 1 day. Participants with acute suicidality as per the ASQ will then be excluded or withdrawn from the study.

### Trial Management

To foster an environment where the participants feel comfortable, the web-based MSC-T intervention will be conducted with groups of 12-18 participants of the same age group [18]. To ensure that there is no exclusion of youth based on socioeconomic status or access to technology, participants who do not have a computer, laptop, tablet, or webcam to attend the web-based sessions will be loaned a study tablet, and mobile internet devices will be provided to those who do not have high-speed internet at home. All participants will receive a subsidy to offset the cost of increased home internet use for the duration of the study. To maximize participant engagement, the trial coordinator will provide weekly reminders for the duration of the program through SMS text messages or email, depending on the participant’s preference.

At each follow-up visit (Table 3), the study coordinator will review the interim medical history using a study case report form and have the participants complete the study questionnaires.

**Table 3 table3:** Schedule of activities.

Procedures	Baseline	8 weeks (±2 weeks)	3 months (±2 weeks)	6 months (±4 weeks)	12 months (±4 weeks)
Informed consent	✓				
Baseline demographics questionnaire	✓				
Problem Areas in Diabetes-Teen version (diabetes distress)	✓	✓	✓	✓	✓
Self-compassion Scale for Youth (self-compassion)	✓	✓	✓	✓	✓
Intervention satisfaction survey^a^		✓			
Patient Health Questionnaire (depression and suicidality)	✓	✓	✓	✓	✓
Generalized Anxiety 7-item scale (anxiety)	✓	✓	✓	✓	✓
Diabetes Eating Problem Survey-Revised version (eating disorders)	✓	✓	✓	✓	✓
Hemoglobin A_1C_	✓				✓
Time in range	✓	✓	✓	✓	✓
Review interval medical history	✓	✓	✓	✓	✓

^a^The intervention satisfaction survey will be given to the participants in the mindful self-compassion for teens (MSC-T) intervention group only.

### Engagement of People With Lived Experience of T1D

To ensure that this study is feasible, interesting, and relevant to youth with T1D, we have engaged and plan to continue to engage with people with lived experience throughout all stages of the study. We have 2 people with lived experience as collaborators (SH and OI), both of whom are former patients of the CHEO diabetes clinic, who will help spearhead engagement strategies. Multimedia Appendix 1 provides more information about our people with lived experience engagement activities.

### Equity, Diversity, and Inclusion Considerations

We have considered gender and diversity in all aspects of this study, from recruitment through to knowledge translation. Multimedia Appendix 2 [4-6,50-52] provides more information about our equity, diversity, and inclusion considerations.

### Statistical Plan

#### Sample Size

Our target sample size is 70 participants per group (140 participants total). This sample size achieves 80% power to detect group differences of 12 points or more [53] using a 2-sided significance level of 5% [26]. In this calculation, we assumed a mean PAID-T score of 73 in the waitlist control group with a SD of 26 [54]. A 30% attrition rate, based on previous relevant trials [55], was also considered.

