### Randomization Procedures

We will use the randomization module in REDCap [21,22] to allocate participants to their group. The randomization table will be created by a study team member who is not directly involved in patient recruitment or data collection using R (R Core Team) [24]. The trial coordinator will generate the allocation for each participant following obtaining informed consent and completion of the baseline assessments (ie, there will be hidden allocation).

Participants will be randomly allocated to either the MSC-T intervention group or the waitlist control group using a 1:1 ratio block randomization. We will stratify each block by age group (12-14 years [early adolescence] or 15-17 years [middle adolescence]). The cohort will be divided by these age groups to deliver the intervention with the goal of fostering a developmentally appropriate and open environment. Stratification by age group is therefore necessary to ensure an equal age distribution between the treatment groups, since the developmental age of a participant could impact their response to the intervention [25]. We will also randomly vary the block size, with blocks of either 6 or 8, to prevent prediction of group allocation as participants are accrued [26].

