#### Secondary Bayesian Analysis for the Primary Outcome

Although our trial is powered to detect a moderate effect size of 12 points on the PAID-T, we acknowledge that a smaller effect size is still clinically meaningful. Bayesian methods focus on providing plausible values for the intervention effect that are compatible with both the observed data and previous knowledge and beliefs. Bayesian analysis enables the use of both noninformative priors that minimize the influence of priors on the statistical inference and informative priors that are guided by existing evidence or a range of collective expertise from investigators regarding the belief or skepticism of the intervention’s efficacy. Thus, a secondary Bayesian analysis will complement our frequentist analysis in the interpretation of our randomized trial results [57]. Following existing Bayesian analysis reporting guidelines [58], we will conduct a prespecified Bayesian linear regression analysis to examine the probability that the MSC-T intervention reduces DD in a clinically meaningful way compared with the control group based on the trial results.

The main objective of the Bayesian analysis is to determine the posterior probability (also known as an updated probabilistic belief) that the MSC-T intervention (1) affects PAID-T scores and (2) reduces DD by between-group differences on the PAID-T of 7-15 points (eg, effect size of 0.27-0.5), given the prior distributions of the treatment effect and the observed data from the trial. We considered an effect size of 0.27 as the minimum threshold for potential clinical relevance, given the strong relationship between DD and clinical outcomes [3], and based on the expert opinions of our team of experienced diabetologists.

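### The stated 80% power for 12 points does not follow from the stated inputs: 70 per group gives about 77% with no dropout and about 62% after the plan's own 30% attrition

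*Protocol article*

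**What the plan says.** The Sample Size section of the protocol article sets a target of 70 participants per group, 140 in total, and states that "This sample size achieves 80% power to detect group differences of 12 points or more" at a two-sided 5% level. It lists its assumptions: "we assumed a mean PAID-T score of 73 in the waitlist control group with a SD of 26". It then adds: "A 30% attrition rate, based on previous relevant trials [55], was also considered". Allocation is 1:1 (Randomization Procedures). The primary analysis is a linear regression of 3-month PAID-T on group, adjusted for age and baseline distress (Primary Analysis for the Primary Outcome). The Bayesian section relies on the same claim: "Although our trial is powered to detect a moderate effect size of 12 points on the PAID-T".

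**The concern.** The section supplies everything needed to compute power for a comparison of two means: group size, difference, SD, significance level and attrition. Read together, they do not produce 80%. The 30% attrition is said to have been taken into account, so 70 should be the inflated number, leaving about 49 per group for analysis. On that reading the shortfall is large.

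This is the power claim for the primary outcome. If the trial gives a null or borderline result, readers will judge it against an 80% chance of detecting 12 points, a sensitivity the design does not have on its own figures. The Bayesian section then repeats the claim as established, to contrast the 12-point target with the smaller effects that analysis is meant to address.

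**Working it through.** **Inputs from the article.** Difference 12; SD 26; two-sided alpha 0.05; target power 0.80; 70 per group, 1:1; attrition 30%. The standardised difference is 12/26 = 0.4615.

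**1. Sample size for 80% power, unadjusted.** Normal approximation: n = 2 × (1.960 + 0.842)² × (26/12)² = 73.7, so 74 per group. The t-test (noncentral t) gives 74.7, so 75 per group. Both exceed 70 before any dropout. Dividing by 0.70 gives 74/0.70 = 105.7, so 106 per group, or 75/0.70 = 107.1, so 108 per group (t-test).

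**2. Power at the stated size, unadjusted.** The standard error of the difference is 26 × √(2/n).

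| Analysed per group | Standard error | 12 / standard error | Power, normal | Power, t-test | Difference detectable at 80% (t-test) |
|---|---|---|---|---|---|
| 70 (no dropout) | 4.39 | 2.73 | 78.0% | 77.4% | 12.4 points |
| 49 (= 70 × 0.70) | 5.25 | 2.28 | 62.7% | 61.9% | 14.9 points |

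**3. Attempts to reproduce 70 per group at 80%** (normal approximation).
- One-sided 5% test: 59 per group before attrition and 85 after; power is 86% at 70 and 74% at 49.
- Inflating by the wrong factor, n × 1.3: 97 per group two-sided, 77 one-sided.

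None of these gives 70.

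**4. Credit for baseline adjustment.** If r is the correlation between baseline and 3-month PAID-T, the adjusted analysis works with a residual SD of 26 × √(1 − r²). With 49 per group and 94 residual degrees of freedom (98 participants less four coefficients):

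| r | Residual SD | Power at 49 per group |
|---|---|---|
| 0.3 | 24.8 | 66% |
| 0.4 | 23.8 | 69% |
| 0.5 | 22.5 | 74% |
| 0.6 | 20.8 | 81% |
| 0.7 | 18.6 | 89% |

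Power reaches 80% at r = 0.59 (0.58 by the normal approximation), where the residual SD is about 21. So 70 per group, 30% attrition and 80% power agree only if a correlation near 0.59 was used. The article gives no correlation and no residual SD.

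**The case against.** The strongest reply is that the 62% and 77% belong to an unadjusted test that the trial will not run. The planned model adjusts for baseline distress, and at r of about 0.59 the stated size, attrition and power fit together exactly. The authors may have used such a value, and a short article could have left it out. Part of this stands: it cannot be said that the trial is certainly underpowered. It does not rescue the text. The section names the assumptions of the calculation, and SD 26 is given as the SD of the scores themselves. Nothing points to a residual SD near 21. The lower end of the effect range in the Bayesian section also uses the unadjusted SD: 7/26 = 0.27. The problem is therefore not a missing detail but a stated result that the figures beside it do not support.

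A second reply is that the 30% has no time point. Follow-up lasts 12 months and the primary outcome is at 3 months, so fewer may be lost by then. That is fair and narrows the gap. If 20% were lost by 3 months (an assumption), 56 per group would remain, with 68% power unadjusted and about 80% at r = 0.5. Timing alone cannot close the gap, since zero loss still gives only 77%.

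Third, the shortfall with no dropout is small, two to three percentage points. Agreed; the material part is attrition.

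Finally, recruitment is complete and a null result can be read from the confidence interval and the planned posterior probabilities. That limits the harm, but does not make the printed power figure correct.

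**Conclusion.** The concern holds. On the inputs the article lists, 70 per group does not give 80% power for 12 points. It gives about 77% with no loss and about 62% after 30% attrition, roughly 18 percentage points short; 80% power then corresponds to about 15 points. These figures assume an unadjusted two-sided comparison, SD 26 in both groups, and the full 30% missing at 3 months. Under the planned baseline-adjusted model the claim could be true at 30% attrition, but only with r of about 0.59 or higher, and the document offers no such value. The 141 participants enrolled, against a target of 140, do not change this.

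**What to change.** Correct the power statement in one of two ways, depending on how the calculation was done.

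- **If baseline adjustment was assumed:** state the baseline-to-3-month correlation (or residual SD) used, with its source, and show power for r from 0.4 to 0.7 at 49 per group (69% to 89%). State that about 0.59 is the least that supports 80%.
- **If it was not:** report that 70 per group with 30% attrition leaves 49 per group, which gives about 62% power for 12 points unadjusted, and that 80% power corresponds to about 15 points.

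In either case, say whether the 30% refers to 3 or 12 months. If the 3-month figure is lower, give the power for it. Amend the opening sentence of the Secondary Bayesian Analysis section to match.

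The cost is wording only: no further enrolment and no change to the planned analysis. The stated power becomes less favourable unless a correlation of about 0.59 or more can be supported.

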#### Statistical Analysis

For the MSC-T and waitlist control groups, the following will be summarized using descriptive statistics: participant baseline characteristics, mental health outcome measures, and self-compassion score responses from each study time point, and for the MSC-T group, we will summarize the results of the intervention satisfaction survey and session attendance.

Our main analyses will be performed based on the intention-to-treat principle. We will also complete per-protocol analyses where we will exclude participants based on nonadherence to the intervention (defined as attending fewer than 6 out of 8 MSC-T sessions, in line with previous work done using MSC-T [56]).

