#### Waitlist Control Group

Participants in the wait-list control group will receive standard-of-care treatment as usual. Following the conclusion of the experimental protocol, participants in this group will be given the opportunity to complete the 8-week web-based MSC-T program.

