#### Primary Analysis for the Primary Outcome

The primary outcome will be analyzed using a linear regression model adjusted for age and baseline DD to assess the effect of the MSC-T intervention on DD at the 3-month time point. We will adjust for age to account for the variability in the developmental stage of each participant, which may impact their response to the mindful self-compassion (MSC) program. We will also account for baseline levels of DD as we are assessing the change in DD from baseline to 3 months.

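### The supplementary per-protocol analysis can drop low attenders only from the MSC-T arm, so it is liable to selection bias in either direction and does not estimate the effect of attending

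*Protocol article*

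**What the plan says.** The Statistical Analysis section of the protocol article puts intention to treat first: "Our main analyses will be performed based on the intention-to-treat principle". It then adds per-protocol analyses that will "exclude participants based on nonadherence to the intervention (defined as attending fewer than 6 out of 8 MSC-T sessions". The same section says that "for the MSC-T group, we will summarize the results of the intervention satisfaction survey and session attendance", so attendance is recorded in that arm.

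The Waitlist Control Group section says: "Participants in the wait-list control group will receive standard-of-care treatment as usual". It continues: "Following the conclusion of the experimental protocol, participants in this group will be given the opportunity to complete the 8-week web-based MSC-T program".

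The primary model is a "linear regression model adjusted for age and baseline DD" (Primary Analysis for the Primary Outcome). The article names no other covariates for the per-protocol analyses, no matching restriction on controls, and no estimator that uses allocation as an instrument.

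**The concern.** The article does not say that the exclusion applies to one arm, but no other workable reading exists. Controls have no sessions to attend before their follow-up ends, and applying the threshold to them would empty the arm. The rule therefore selects on behaviour after randomisation in the MSC-T arm and leaves the control arm whole. Controls who would have attended poorly stay in; their MSC-T counterparts are removed.

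Age and baseline distress are the only stated adjustments. Motivation, mood, family support and social context could all influence both attendance and the 3-month score. If the per-protocol difference came out larger than the intention-to-treat difference, it could be taken to show that the programme works when attended, although it might show only who attends.

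**Working it through.** The plan states no figure for the per-protocol analysis, so there is none to reproduce. The check has two parts: an identity for the bias, and a second calculation under a different model.

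**Inputs from the protocol article.** PAID-T SD 26 and 70 participants per group (Sample Size); exclusion below 6 of 8 sessions (Statistical Analysis); adjustment for age and baseline distress (Primary Analysis for the Primary Outcome); an effect size of 0.27, about 7 points, as the smallest effect of potential clinical relevance (Secondary Bayesian Analysis for the Primary Outcome).

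**Assumptions not in the documents.** The share of low attenders p; the gap g in untreated 3-month score (low attenders minus attenders) left after adjustment; and, for the second calculation, the baseline-outcome correlation r and the correlation rho between attendance and residual prognosis. The per-protocol model is assumed to carry the primary model's covariates.

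**1. Identity.** Write Y0 for the score without the programme. Randomisation makes the control mean equal to (1 - p) x mean Y0 of attenders + p x mean Y0 of low attenders. Attenders' mean Y0 minus the control mean is therefore -p x g. This is added to whatever effect attenders truly receive. Lower PAID-T is better, so a positive g favours MSC-T and a negative g works against it.

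| p | g = 0.25 SD (6.5 points) | g = 0.5 SD (13 points) |
|---|---|---|
| 0.15 | 0.15 x 6.5 = 0.98 | 0.15 x 13 = 1.95 |
| 0.30 | 0.30 x 6.5 = 1.95 | 0.30 x 13 = 3.9 |
| 0.40 | 0.40 x 6.5 = 2.6 | 0.40 x 13 = 5.2 |

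The range is about 1.0 to 5.2 points. If g is 0, the bias is 0; if g is negative, the sign reverses.

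**2. Second model.** The true effect is set to 0 and r to 0.6, so the residual SD is 26 x sqrt(1 - 0.36) = 20.8. Attendance is a threshold on a normal variable that has correlation rho with better residual prognosis. Low attenders are dropped from the MSC-T arm only, and the score is regressed on group and baseline. In closed form, bias = -20.8 x rho x phi(z_p)/(1 - p). For p = 0.30 and rho = 0.3 this is -20.8 x 0.3 x 0.497 = -3.1. A simulation of 400,000 participants per setting agreed closely with the formula, and its intention-to-treat estimate stayed at about 0.

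| p | rho = 0 | rho = 0.1 | rho = 0.3 | rho = 0.5 |
|---|---|---|---|---|
| 0.20 | 0 | -0.7 | -2.2 | -3.6 |
| 0.30 | 0 | -1.0 | -3.1 | -5.2 |
| 0.40 | 0 | -1.3 | -4.0 | -6.7 |

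With 70 randomised per arm and no attrition, the nominal 5% per-protocol test rejected a true null at these simulated rates:

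| p | rho = 0 | rho = 0.3 | rho = 0.5 |
|---|---|---|---|
| 0.20 | about 5% | 8% | 16% |
| 0.30 | about 5% | 12% | 27% |
| 0.40 | about 5% | 17% | 38% |

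Both calculations show that the exclusion does no harm only when attendance carries no information about prognosis beyond the covariates.

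**The case against.** **The analysis is supplementary.** No objective or hypothesis rests on it, and the article never calls it an effect of adherence. This stands: the intention-to-treat result is untouched, and harm arises only if the per-protocol figure is interpreted causally.

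**Bias is assumed, not shown.** A reader might infer that the rule certainly biases the estimate in favour of MSC-T because attenders are better motivated or better functioning. The documents do not support that. They report no attendance rate and no link between attendance and prognosis. More distressed adolescents might attend more, which would reverse the sign. Reminders, loaned tablets and mobile internet (Trial Management) are meant to sustain attendance, so a 40% share of low attenders has no anchor in the plan. The upper end is also demanding: at r = 0.6, a 13-point gap is 13/20.8 = 0.63 residual SD, which needs rho of about 0.4.

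**The 7-point yardstick is borrowed.** The article sets it for the Bayesian analysis of the primary outcome, not for this analysis. It gives scale and nothing more.

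**The alternative has its own weaknesses.** In its binary form a complier-average effect is roughly the intention-to-treat estimate divided by the attending share, so it is larger in magnitude by construction: 7 points with 70% attending gives 7/0.7 = 10. It also needs allocation to act only through attendance. Participants are unblinded (Strengths and Limitations) and outcomes are self-reported (Safety Parameters and Description of Risk), so that is open to doubt. Two-stage least squares does not by itself recover people without a 3-month score, and the plan allows for 30% attrition. These points stand. They argue for stating the assumptions openly, and they make it debatable whether the exclusion analysis must be dropped altogether.

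**A condensed article leaves detail to the analysis plan.** True of covariates and labels, but the exclusion variable and threshold are stated here, and selection on attendance in one arm follows from them.

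**Conclusion.** The point holds in a limited form. The stated rule can act on the MSC-T arm only, so the per-protocol analysis compares selected attenders with all controls. It is liable to selection bias in either direction unless attendance is unrelated to the 3-month PAID-T score given age and baseline distress. The 1.0-5.2 points are an illustration that rests wholly on the assumed shares and gaps; the second model gives about 0.7-6.7 points for rho from 0.1 to 0.5, and none at rho = 0. The documents do not show that bias will occur, how large it would be or which arm it would favour, and nothing here weakens the intention-to-treat conclusion. The change is worth making because it is cheap and because a per-protocol result that differs from intention to treat would have no clear interpretation.

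**What to change.** Make a complier-average causal effect the adherence estimate. Use two-stage least squares with random allocation as instrument, adjusted for age and baseline PAID-T. Include all randomised participants who have a 3-month score, with the same missing-data handling as the intention-to-treat analysis. Controls have no access during follow-up, so non-compliance is one-sided and the method suits the design.

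- First version: sessions attended (0-8) as the exposure, so that partial attendance counts. This assumes a linear effect per session.
- Second version: attendance of at least 6 of 8 sessions. This assumes no effect below 6 sessions.
- Both versions: state that allocation is assumed to act only through attendance, and that this is questionable with unblinded, self-reported outcomes.

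If the exclusion-based analysis is kept, label it descriptive and do not interpret it as the effect of attending.

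The cost is a few lines in the analysis plan, using attendance that is already recorded. The downside is a wider interval and reliance on the exclusion restriction.
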